### Data collection

The surgeons will screen all patients for trial eligibility during preoperative surgical consultation. All patients will undergo preoperative assessment the day before surgery, including a medical interview and recorded audit by a trained research team. Components of the patient interview are resumed by: 1/sociodemographic data, 2/information regarding to tobacco use, alcohol abuse, impairment of hearing and vision, 3/medical past and comorbidities, 4/assessment of pain using the NRS [25]; 5/assessment of nutritional status using the MNA [26]; 6/assessment of self-care functions using the ADL [27] and the IADL [28]; 7/assessment of cognitive and depression status using the MMSE [30] and the Mini-GDS [31]; 8/delirium assessment using CAM [32,33]. Data about past medical, biology results, surgery (type, duration, complications during surgery) and anesthesia (type of anesthesia - general versus regional, anesthetic drug used) will be obtained from the medical file by research team.

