**Method/Design:**

Study design is a stepped wedge cluster randomized trial within 3 surgical wards of three French university hospitals. All patients aged 75 and older, and admitted for scheduled surgery will be included. The multifaceted program will be conducted by mobile geriatric team, including geriatric preoperative consultation, training of the surgical staff and implementation of the *Hospital Elder Life Program*, and morbidity and mortality conference related to delirium cases. The primary outcome is based on postoperative delirium rate within 7 days after surgery. This program is planned to be implemented along four successive time periods within all the surgical wards. Each one will be affected successively to the control arm and to the intervention arm of the trial and the order of program introduction within each surgical ward will be randomly assigned. Based on a 20% reduction of postoperative delirium rate (ICC = 0.25, α = 0.05, β = 0.1), three hundred sixty patients will be included i.e. thirty patients per service and per time period. Endpoints comparison between intervention and control arms of the trial will be performed by considering the cluster and time effects.

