## Methods/Design

### Study design

CONFUCIUS protocol is based on a stepped wedge trial design, which is appropriate in assessing the impact of patient safety interventions [23,24]. It is an original design of cluster randomised controlled trial (figure 1). In the CONFUCIUS trial, the multifaceted prevention program will be rolled-out sequentially to three surgical wards (clusters) over four time periods (steps). The order in which the different surgery wards will receive the program is determined at random, allowing the full implementation of intervention in all participating clusters by the end of the trial [24]. Stepped wedge design also has strong methodological value to reduce contamination bias, considering that each cluster acts as its own control and hence provides data in both control and intervention arms of the trial [24].

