### Setting and patients

The CONFUCIUS trial will take place in 3 surgical wards (orthopaedic, digestive and urology surgery) of 3 distinct French university hospitals. Each hospital benefits from its own MGT, which is composed of geriatricians and nurses. All health professionals in the participating surgical wards will be involved to conduct the multidisciplinary prevention program (i.e. surgeons, anaesthetists, nurses, and nurse assistants).

Inclusion criteria are age 75 and older, admission for a scheduled surgery (i.e. respectively colorectal cancer, ureterostomy, nephrectomy or cystectomy, total hip or knee replacement), participation agreement and no psychiatric trouble.

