#### 2/Training of the surgical wards staff and implementation of the Hospital Elder Life Program (HELP)

All members of medical and nursing staffs will attend a two hours training session performed by the MGTs in their surgical ward. This training will focus on post-operative delirium issues (diagnosis, frequency, seriousness, and risk factors) and the HELP presentation [16]. This non pharmacological program focuses on patient spatiotemporal orientation, including: 1/to promote the use of appropriate glasses and hearing aids; 2/to encourage to bring personal belongings; 3/to encourage proxies to visit the patient during his hospital stay; 4/to set up clocks and calendars in patients room; 5/to adjust the luminosity according on the time of the day; 6/to improve patient implantation in the current reality (for example, telling about the time and the date during medical and nursing cares).

All these recommendations will be reminded by posters on the wall of patient rooms in surgical wards and explained by brochures provided to proxies.

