### Ethical consideration

The participating patients will give their verbal informed consent after being told about the study. Their participation or refusal will not affect their medical and nursing care. The study protocol has been reviewed and approved by an ethics committee (Comité de Protection des Personnes Sud-Est IV). All procedures are in accordance with the declaration of Helsinki.

CONFUCIUS study has been registered in the clinical trials (Current Controlled Trials NCT01316965).

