The CONFUCIUS study is based on an original methodology. Stepped wedge trial design is a particular cluster randomised controlled study design which is useful for evaluation of patient safety interventions [23,24]. This design differs from both parallel and cross-over designs. With stepped wedge design, intervention is introduced to participants sequentially so that, by the end of the study, all participants are exposed to the intervention [23,24]. The three main motivations for using a stepped wedge design are ethical, logistical and statistical [23,24]. (1) From an ethical point of view, if the hypothesis is that the intervention will do more good than harm, it might be considered unethical to exclude any participants from the program. (2) Stepped wedge design is also particularly useful when, for logistical reasons, it is not possible to implement an intervention to all participants simultaneously. (3) Furthermore the stepped wedge design has statistical advantages. First, surgical wards act as their own control and hence provide date points in both control and intervention units [23,24]. This feature of the stepped wedge design reduces the risk of bias, which may be most important in non-randomised studies. Second, the effects of time can be included in the statistical model, hence controlling for temporal changes in the effectiveness of the program [23,24].

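### Surgeons who take part in the programme screen patients after the ward-period's condition is set, so selection could change at crossover and mimic or hide a programme effect

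*Protocol article*

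**What the plan says.** All references are to the protocol article.

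- **Randomisation (Study design).** "The order in which the different surgery wards will receive the program is determined at random". Patients are recruited afterwards, within ward-periods whose condition is already set.
- **Screening (Data collection).** "The surgeons will screen all patients for trial eligibility during preoperative surgical consultation".
- **The surgeons' role (Setting and patients).** "All health professionals in the participating surgical wards will be involved to conduct the multidisciplinary prevention program (i.e. surgeons, anaesthetists, nurses, and nurse assistants". The intervention section on staff training adds: "All members of medical and nursing staffs will attend a two hours training session performed by the MGTs in their surgical ward".
- **Entry criteria (Setting and patients).** Besides age and named scheduled operations, entry needs "participation agreement and no psychiatric trouble". The psychiatric criterion is not defined.
- **Consent (Ethical consideration).** "The participating patients will give their verbal informed consent after being told about the study". The person who obtains it is not named.
- **Stated intent (abstract, Method/Design).** "All patients aged 75 and older, and admitted for scheduled surgery will be included".
- **Baseline data and adjustment.** Data collection has a trained research team assess comorbidity, nutrition, function, cognition, mood and delirium status before surgery. Statistical analysis plans multivariable adjustment for patient characteristics.
- **The design's protection (Discussion).** Of wards acting as their own control, the article says: "This feature of the stepped wedge design reduces the risk of bias".

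**The concern.** Randomising the order of wards protects the comparison only if patients enter in the same way before and after crossover. Here the screeners know which condition applies, because they help deliver it. Two things change for them at crossover. They are trained in delirium and its risk factors, and trial entry now brings a geriatric consultation for the patient. Either could alter who is judged free of psychiatric trouble or who agrees to take part.

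If fewer frail or cognitively impaired patients enter in programme periods, the observed delirium rate falls without any programme effect. If more enter, because they seem good candidates for geriatric input, a real effect is hidden. With three wards, a change in one ward's recruitment carries much weight.

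**Working it through.** **1. The passages side by side.** The condition is set by ward and period (Study design). Screening follows, patient by patient, by staff who know the condition (Data collection; Setting and patients; the staff training section). Two entry criteria depend on judgement or agreement (Setting and patients). These statements are enough to make differential selection possible. They do not show that it will occur.

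**2. Whether the design removes it.** Write the outcome as ward effect + period effect + programme effect × indicator + selection shift. If selection changes when a ward crosses over, the shift has the same pattern as the indicator. The ward's own control periods lack the shift and its programme periods carry it, so the within-ward comparison keeps it. Period effects common to all wards cannot absorb it, because wards cross over at different times.

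**3. Illustration of size.**

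From the document (Sample size): control rate 0.60, programme rate 0.40, so the planned effect is 20 points. The planned total reproduces as 3 wards × 4 periods × 30 = 360, but the point does not rest on it.

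Assumed, not in the document: 30% of eligible patients are high-risk, with a delirium rate of 80%. There is no programme effect and no covariate adjustment.

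- Rate r in the remaining 70%: 0.30 × 0.80 + 0.70 × r = 0.60, so r = 0.36/0.70 = 0.514.
- One third of high-risk patients not enrolled: (0.20 × 0.80 + 0.36)/0.90 = 0.52/0.90 = 0.578. This is a fall of 2.2 points, or 11% of the planned effect.
- One half not enrolled: (0.15 × 0.80 + 0.36)/0.85 = 0.48/0.85 = 0.565. This is a fall of 3.5 points, or 18% of the planned effect.

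A wider set of assumptions gives a wider range. If high-risk patients have 80% delirium and the others 50%, a fall of 10 to 30 percentage points in the high-risk share gives a spurious reduction of 0.30 × 10 = 3 to 0.30 × 30 = 9 points. If the others have 40%, it is 4 to 12 points.

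**4. Effect on the false-positive rate.** Figure 1 is not shown, so I assume one ward crosses over at each of periods 2, 3 and 4. With 30 patients per ward-period, residual variance 0.60 × 0.40 = 0.24 and the abstract's ICC of 0.25, weighted analysis of ward-period means gives a standard error (SE) of about 0.097 with period effects and 0.056 without. The two-sided 5% error rate under a bias b is Φ(−1.96 + b/SE) + Φ(−1.96 − b/SE).

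| Bias | With period effects | Without period effects |
|---|---|---|
| 2.2 points | 0.056 | 0.068 |
| 3.5 points | 0.065 | 0.096 |

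The inflation is modest in these scenarios.

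**The case against.** The strongest reply is that the article states an all-comers intent. Every patient is to be screened, the abstract says all patients of the required age having scheduled surgery enter, and eligibility is tied to age and named operations. That limits discretion over who is considered, and it stands. It does not close the gap, because agreement and the undefined psychiatric criterion qualify the intent.

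A second reply is that a shift would be visible and adjustable. The research team records cognition, function, nutrition, mood and comorbidity, which are the traits at issue. This largely stands. A reader might infer that nothing planned would reveal the selection, and the document does not support that. The limit is that these data cover only enrolled patients, and adjustment handles only what is measured.

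Three further readings go beyond the text:

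- **That surgeons also enrol patients or take consent.** The article says only that they screen. Screening alone is enough for the concern.
- **That conferences treat every delirium case as a programme failure, giving surgeons a motive to avoid high-risk patients.** The conference section says that records of delirium cases are analysed to find and address failures. It does not class each case as one.
- **That the bias could reach 8.6 points (60% to 51.4%).** Under the assumptions above, this needs every high-risk patient to be left out in programme periods, which nothing in the article suggests.

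The Discussion's sentence on own controls is not an error either. It claims that bias is reduced, not that recruitment bias is removed. Finally, the lack of a screening log in a journal article is no fault in itself, since the full protocol may contain one.

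**Conclusion.** The point holds as a risk created by a stated procedure: screening is assigned to staff who know the condition, after it is set, with two criteria open to judgement. A change in selection at crossover would be aligned with the programme, and neither own-control comparison nor common period effects would remove it. Measured baseline data and adjustment would reveal and correct part of it.

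The direction cannot be known in advance. For size, about 2 to 3.5 points out of a planned 20 is a reasonable illustration. It rests on an assumed 30% high-risk share, an assumed 80% delirium rate in that group and no adjustment, so the adjusted figure would probably be smaller. A reader might infer that the trial's result would be invalid or that biased selection is likely. The document supports neither. It supports tightening the screening step while that is still cheap.

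**What to change.** Change the screening sentence under Data collection so that, in every period and both conditions:

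- the existing research team identifies candidates consecutively from the surgical booking list, by age 75 or older and the named procedures;
- one fixed written definition of the psychiatric criterion, set by the investigators, is applied throughout;
- the same consent wording is used;
- age, sex, procedure and reason (refused, psychiatric criterion, not approached) are logged for each listed patient not enrolled.

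Report the enrolled/eligible fraction and the baseline characteristics by ward-period.

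The cost is a change of wording, a one-line entry per listed patient and some list-checking time. The research team's described contact is the day before surgery, so list checking would have to start earlier.

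This reduces selection but does not remove it. Research staff are not shown to be blind to condition, and a research assistant audits programme components in the patient's room. The booking list still follows from surgeons' decisions, and agreement remains individual. Information on patients not enrolled is hard to rebuild later, so the log should start with the first control period.

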### Sample size

Sample size calculation was inspired from the methodology of Hussey and Hughes [23] and based on the following hypothesis: 1/three surgical wards (clusters) over four successive time periods, 2/improvement of at least 20% regarding primary outcome after the program implementation (from 60% to 40%) [1,16,19], 3/alpha fixed at 5%, 4/a number of patients per time period ranging from 60 to 120, 5/a coefficient of variation or intracluster correlation coefficient (ICC) ranging from 0 to 0,4. The ICC is a measure of the relatedness of clustered data by comparing the variance within clusters with the variance between clusters. Table 2 presents the statistical power obtained according to various values for ICCs and numbers of patients per time period. At least 90 patients per time period, i.e. 30 per time period and per surgical ward will be necessary to obtain a statistical power greater than 90%. Consequently, 360 patients will be included in the study. The time period duration will be 6 months to ensure the inclusion of 30 patients per time period and per surgical ward.

**Table 2 T2:** Statistical power calculated from intracluster correlation coefficients (ICC) and numbers of patients per time period

ICC	60 patients per time period	90 patients per time period	120 patients per time period
**0**	0.95	0.99	1

**0.1**	0.87	0.96	0.99

**0.2**	0.84	0.95	0.98

**0.3**	0.83	0.94	0.98

**0.4**	0.83	0.94	0.98

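### The claimed power above 90% with 360 patients is wrong: 30 patients per ward per period give about 54% at the planned ICC, and Table 2 fits only if its columns are per-ward counts

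*Protocol article*

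**What the plan says.** The Sample size section describes its approach this way: "Sample size calculation was inspired from the methodology of Hussey and Hughes". It assumes "three surgical wards (clusters) over four successive time periods", a fall in delirium from 60% to 40%, alpha of 5%, between 60 and 120 patients per period, and "a coefficient of variation or intracluster correlation coefficient (ICC) ranging from 0 to 0,4".

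Table 2 is titled "Statistical power calculated from intracluster correlation coefficients (ICC) and numbers of patients per time period". Its columns are headed 60, 90 and 120 patients per time period. The 90 column reads 0.99, 0.96, 0.95, 0.94 and 0.94 for rows 0, 0.1, 0.2, 0.3 and 0.4.

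The text divides 90 by three wards and concludes that "30 per time period and per surgical ward will be necessary to obtain a statistical power greater than 90" per cent. The total is then 30 × 3 × 4 = 360. The Abstract (Method/Design) repeats that "three hundred sixty patients will be included i.e. thirty patients per service and per time period", with ICC 0.25 and beta 0.1, and says that arms will be compared with allowance for cluster and time effects.

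**The concern.** The first row of Table 2 has no clustering, so it can be checked against an ordinary two-group comparison. Read as the text reads it, the 60 column is 60 × 4 = 240 patients, or 120 per arm. A plain comparison of 60% with 40% at that size, with no cluster or period terms, has two-sided power of 0.885. Table 2 prints 0.95. Period effects can only lower the figure, so the table cannot have been computed for the sizes in its headings as the text interprets them.

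The total of 360 and the claim of beta = 0.1 both rest on this table. If the column sizes are really per ward, the trial has one third of the patients behind its stated power and close to even odds of missing its own target effect. A null result could then be wrongly read as evidence against the programme.

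**Working it through.** **Inputs.** From Sample size: I = 3 wards, T = 4 periods, rates 0.60 and 0.40 (difference 0.20), alpha 5%. From the Abstract: ICC 0.25, beta 0.1, cluster and time effects considered. Assumed: a two-sided test; within-ward variance 0.24 (0.6 × 0.4); and the layout 0111 / 0011 / 0001. Figure 1 is not shown, so the layout is inferred from Study design, which describes randomised sequential introduction "allowing the full implementation of intervention in all participating clusters by the end of the trial".

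**Formula (Hussey–Hughes, with period effects).** With n patients per ward per period, s = 0.24/n and between-ward variance τ²:

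Var = I·s·(s + Tτ²) / [(IU − W)s + (U² + ITU − TW − IV)τ²]

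For this layout:
- U = 6 (intervention ward-periods)
- W = 0² + 1² + 2² + 3² = 14 (squared period totals)
- V = 3² + 2² + 1² = 14 (squared ward totals)
- IU − W = 18 − 14 = 4
- U² + ITU − TW − IV = 36 + 72 − 56 − 42 = 10

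So Var = 3s(s + 4τ²)/(4s + 10τ²), and power = Φ(0.20/√Var − 1.96).

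**Step 1: reproduce Table 2.** Take n = 60, 90, 120 per ward per period and τ = CV × 0.60. Example, CV 0.1 and n = 90: s = 0.002667, τ² = 0.0036, Var = 0.008 × 0.017067/0.046667 = 0.002926, SE = 0.0541, power = Φ(3.698 − 1.96) = 0.959 (printed 0.96).

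| Row | n = 60: rebuilt / printed | n = 90: rebuilt / printed | n = 120: rebuilt / printed |
|---|---|---|---|
| 0 | 0.955 / 0.95 | 0.994 / 0.99 | 0.999 / 1 |
| 0.1 | 0.866 / 0.87 | 0.959 / 0.96 | 0.988 / 0.99 |
| 0.2 | 0.837 / 0.84 | 0.948 / 0.95 | 0.985 / 0.98 |
| 0.3 | 0.830 / 0.83 | 0.945 / 0.94 | 0.984 / 0.98 |
| 0.4 | 0.827 / 0.83 | 0.944 / 0.94 | 0.984 / 0.98 |

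The largest difference is 0.005. If the row is taken as a true ICC, row 0.1 with n = 60 gives 0.83 against the printed 0.87. A CV of 0.4 at a rate of 60% gives τ² = 0.24² = 0.0576 and an ICC of 0.0576/(0.0576 + 0.24) = 0.19, so the rows cover ICC 0 to about 0.19, not 0 to 0.4.

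**Step 2: the same formula at the planned sizes (20, 30, 40 per ward per period).**

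| Row | As CV: 20 / 30 / 40 | As ICC: 20 / 30 / 40 |
|---|---|---|
| 0 | 0.559 / 0.733 / 0.846 | 0.559 / 0.733 / 0.846 |
| 0.1 | 0.468 / 0.614 / 0.725 | 0.406 / 0.551 / 0.669 |
| 0.2 | 0.417 / 0.561 / 0.678 | 0.396 / 0.542 / 0.662 |
| 0.3 | 0.401 / 0.546 / 0.666 | 0.392 / 0.539 / 0.660 |
| 0.4 | 0.394 / 0.541 / 0.661 | 0.390 / 0.537 / 0.658 |

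Against the printed table, the CV columns are up to 0.44 too low.

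**Step 3: the abstract's ICC of 0.25.** τ² = 0.25 × 0.24 = 0.06 and s = 0.24/30 = 0.008. Var = 0.024 × 0.248/0.632 = 0.009418, SE = 0.0970, power = Φ(2.061 − 1.96) = 0.54. It is also 0.54 if τ² = 0.25 × 0.24/0.75, and 0.55 if 0.25 is a CV.
- Difference detectable with 90% power: (1.960 + 1.282) × 0.0970 = 0.315, or 31.5 points.
- Expected 95% confidence interval half-width: 1.96 × 0.0970 = 0.19, or 19 points.
- Size for 90% power at 20 points: 76 per ward per period, 76 × 12 = 912 patients.
- Size that the 90 column represents: 90 × 12 = 1,080 patients.

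**Sensitivity at 30 per ward per period.** One-sided 5% gives 0.83 down to 0.66. Variance 0.25 gives 0.72 down to 0.52. Two shifted layouts give the same power as the inferred one.

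**The case against.** The strongest reply is that the low figure depends on including period effects. Without them, 30 per ward per period gives 0.972, 0.955, 0.947, 0.945 and 0.944, close to the printed 90 column, and power stays above 90%. The Statistical analysis section names only the cluster effect in the logistic model and mentions time only for the evolution of the intervention effect. In rows 0.2 to 0.4 this rival and the per-ward reading agree to about 0.001, so those nine cells cannot tell them apart.

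The rival still fails. It gives 0.885 where Table 2 prints 0.95 (row 0, 60 patients) and 0.972 where it prints 0.99, so it did not generate the table. It also departs from the cited method and from the Abstract, which plans for time effects, and the Discussion presents control of temporal change as an advantage of the design. In a stepped wedge, time is confounded with intervention, so power obtained by ignoring it is not power for a valid comparison.

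Three qualifications stand. That a per-ward size was divided by three is an inference from the fit; the article does not say so. The 54% belongs to ICC 0.25 and the upper rows; over the whole table the range is 54% to 73%. The CV/ICC label is secondary, since the article half-acknowledges both readings and, at 0.2 and above, the choice moves power at 30 per ward per period by no more than about 0.02.

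**Conclusion.** The concern holds. With 360 patients and period effects in the model, power for 60% against 40% is 0.54 at the abstract's ICC of 0.25 and at most 0.73 when there is no clustering. It is not above 0.90 anywhere in the article's range. Table 2 is reproduced in full only with column sizes per ward per period and a coefficient of variation in the rows, so the planned total is one third of the 1,080 behind the quoted 0.94 to 0.99.

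This rests on a two-sided 5% test, within-ward variance of 0.24, the inferred layout and a normal approximation. With only three clusters, a small-sample correction would lower the power further.

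**What to change.** In Sample size:
- Recalculate Table 2 for 20, 30 and 40 patients per ward per period: 0.56 / 0.73 / 0.85 at ICC 0 and about 0.39 / 0.54 / 0.66 at ICC 0.2 to 0.4.
- State in the column headings that these are counts per ward per period.
- Label the row parameter as either an ICC or a coefficient of variation, and use the same term in the text and the Abstract.
- Replace the claim of power above 90% with about 54% for 60% against 40% at ICC 0.25, and give the detectable difference of about 31 points at 90% power.

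In the Abstract, replace beta = 0.1 accordingly. State, where results will be interpreted, that a non-significant result cannot exclude the 20-point target.

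This costs only wording and a corrected table, with a less favourable stated power. It does not restore the power. If the sponsor wants to keep 90% for a 20-point difference at ICC 0.25, the total is about 912 patients, which is a change of design and not of wording.
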